#### Sample size calculation

2.6.1

Prior ED studies have reported single time-point hs-troponin sensitivities of 97-99% in patients with ≥2 h of symptoms [11]. These sensitivities are considered adequate to safely rule out ACS in primary care [25]. Therefore, we applied a target sensitivity of 98% to calculate the required sample size for our diagnostic accuracy trial, comparing the index test with the reference standard (occurrence of MACE within 6 weeks of the index test). We set a margin of error of 3% around the sensitivity estimate and an alpha of 0.10 (two-sided), reflecting the rule-out focus in primary care. Assuming a MACE prevalence of 7% (literature and historic data range 5-15%), these parameters yield a required 842 participants to ensure adequate statistical power to detect a meaningful diagnostic performance​ in terms of sensitivity. To account for potential drop-out or a lower event rate, we aim to include at least 900 participants. Sample size calculations were performed following the methods of Akoglu, Bujang and Adnan, and calculated using PASS software [[26], [27], [28]]**.**

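### The 842 is a symmetric 90% precision calculation with no power in it, and it understates the lower-side uncertainty of sensitivity at about 59 to 63 events

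*Protocol article*

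**What the plan says.** The protocol article, section 2.6.1 (Sample size calculation), starts from a target: "we applied a target sensitivity of 98% to calculate the required sample size for our diagnostic accuracy trial". It fixes the precision: "We set a margin of error of 3% around the sensitivity estimate and an alpha of 0.10 (two-sided"), and gives the rule-out purpose as the reason for that alpha. The event rate is set as "Assuming a MACE prevalence of 7% (literature and historic data range 5-15"%). The result is then described in terms of power: "these parameters yield a required 842 participants to ensure adequate statistical power to detect a meaningful diagnostic performance", in respect of sensitivity. The target is rounded up: "To account for potential drop-out or a lower event rate, we aim to include at least 900 participants".

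The section refers to published sample-size methods and to PASS but does not print the formula. It gives no null value, no minimum acceptable sensitivity and no power figure. Section 2.6 (Statistical analysis) names sensitivity and negative predictive value for 6-week MACE as the safety measures of the primary analysis. It attaches no hypothesis or success criterion to them.

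**The concern.** Two statements do not fit the calculation behind them.

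First, a margin of error is a precision target. Power needs a value to be excluded and a value assumed true, and only the second is given.

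Second, a symmetric 3-point margin around 98% cannot describe the uncertainty when only one or two events are expected to be missed. The upper side has only 2 points of room, so the uncertainty falls mainly on the lower side. For a rule-out strategy the lower limit of sensitivity carries the safety message. A reader who takes 98 ± 3% at face value expects a lower limit near 95%, and the trial will usually not produce one.

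**Working it through.** **Inputs (section 2.6.1).** Sensitivity 0.98; margin 0.03; two-sided alpha 0.10, so z = 1.645; prevalence 0.07 (range 0.05 to 0.15); N = 842, planned at least 900.

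**1. Reproducing 842.** Events = z² × p(1 − p) / d² = 1.6449² × 0.98 × 0.02 / 0.03² = 58.92. N = 58.92 / 0.07 = 841.7, rounded up to 842. (Rounding the events to 59 first gives 843.) The Wald formula is inferred from this exact match. There is no power term in it.

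**2. Expected counts.** 842 × 0.07 ≈ 59 MACE, with 59 × 0.02 ≈ 1.2 expected misses. 900 × 0.07 = 63 MACE, with about 1.3 expected misses. The implied interval is 0.98 ± 0.03, that is 95% to 101%.

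**3. Realistic results, 90% intervals.**
- 58/59 (98.3%): exact (Clopper-Pearson) 92.2% to 99.9%, lower limit 6.1 points below the estimate; Wilson lower limit 92.75%, 5.6 points below.
- 57/59 (96.6%): exact lower limit 89.7%, 6.9 points below.
- 62/63 (98.4%): exact lower limit 92.7%, 5.7 points below; Wilson 93.2%, 5.2 points below.
- 59/59: exact lower limit 95.05%.

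**4. Average over all possible results at a true sensitivity of 98%.** For each count x, weight (x/n − lower limit) and the half-width by the binomial probability of x, and sum.

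| 90% interval | Mean distance to lower limit, 59 events | Same, 63 events | Mean half-width, 59 events | Same, 63 events |
|---|---|---|---|---|
| Clopper-Pearson | 6.1 points | 5.8 | 3.87 | 3.71 |
| Wilson | 5.6 | 5.3 | 3.45 | 3.31 |
| Jeffreys | 4.7 | 4.5 | 3.05 | 2.94 |

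Subtracting from 98%, the mean lower limit is 91.9% to 92.2% (Clopper-Pearson), 92.4% to 92.7% (Wilson) and 93.3% to 93.5% (Jeffreys).

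**5. Dependence on prevalence (900 enrolled, no drop-out).** At 5%: 45 events, mean exact lower distance 7.6 points. At 15%: 135 events, 3.3 points. The 59 events are kept only if prevalence is at least 59/900 = 6.6%.

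**6. Power, if the margin is turned into a test.** The only lower bound the text implies is 98 − 3 = 95%. For H0: sensitivity ≤ 95% at one-sided 0.05, zero misses are required (0.95^59 = 0.048; 0.95^63 = 0.039; allowing one miss exceeds 0.05). Power at a true 98% is 0.98^59 = 0.304, or 0.98^63 = 0.280. With a null of 90%, which is an assumption and not in the article, power would be about 67% (59 events) or 87% (63 events). The answer depends entirely on a value the article does not give.

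**The case against.** The strongest defence is that a margin of error ordinarily means a half-width, and on that reading the design comes close to its target. The Jeffreys 90% interval covers about 97% (59 events) and 96% (63 events) at a true 98%, and its average half-width is 3.05 and 2.94 points. This stands. A reader might infer that no interval with valid coverage gives a 3-point margin; for half-width that is wrong. What remains is that the half-width is not shared equally between the two sides, and the article's figure does not show it.

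Four other stronger readings are tempting and are not supported:

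- **Alpha 0.10 is too lenient.** The lower limit of a two-sided 90% interval is a one-sided 95% bound, and a rule-out question concerns the lower limit. The article's reason for this alpha is coherent, and nothing requires 95% intervals. All figures above use the article's own 90% level.
- **The trial's interval will cover only 69% of the time.** That is the coverage of a Wald 90% interval at 59 events and a true 98%, mostly because it collapses to a single point when nothing is missed (probability 30%). The article commits to no interval method for the analysis, and that choice may sit in an analysis plan that is not shown. It is a reason to avoid Wald, not evidence that Wald will be used.
- **The trial cannot beat current care, because 8-19% of ACS is missed now.** That figure concerns ACS in other cohorts, whereas the endpoint here is MACE including all-cause death. The comparison with standard care is a secondary analysis. It can use the same patients, because the GP records whether referral would have followed without the test result.
- **The lower limit is always 6 points away.** Six points is the exact-method figure, which is conservative here, at 7% prevalence. Other sound methods give less, and higher prevalence gives much less.

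**Conclusion.** The arithmetic of 842 is correct; two statements attached to it are not. The calculation provides precision only, so the claim "to ensure adequate statistical power to detect a meaningful diagnostic performance" has no basis. On the one reading the text allows, excluding 95%, power is about 30% or less. The symmetric 3-point margin understates lower-side uncertainty: at 59 to 63 MACE the average 90% lower limit lies about 4.5 to 6 points below the estimate, not 3.

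This rests on the Wald formula being the source of 842 (inferred from the exact match), a true sensitivity of 98%, and 7% prevalence with no drop-out. At 5% prevalence the shortfall is larger, and at 15% it nearly disappears. The enrolment target itself is not shown to be wrong, and no stated success criterion would be wrongly met. The correction matters because the figures describe the precision of the trial's main safety result.

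**What to change.** Keep the target of at least 900 participants and make three text changes.

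1. Replace the 3% margin statement with the expected asymmetric interval, for example: *With 59 to 63 MACE and a true sensitivity of 98%, the expected lower limit of the 90% interval is about 92% by the exact method and 92 to 93% by Wilson.* Add that this depends on prevalence, with expected exact lower distances of 7.6 points at 5% and 3.3 points at 15%.
2. Delete the power claim and describe the calculation as precision-based.
3. Use an exact, Wilson or Jeffreys interval for sensitivity and NPV, not Wald, and choose it before the data are analysed.

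The cost is a few sentences and no additional patients. The drawback is that the stated precision becomes less favourable.

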### Safety and monitoring

2.7

To ensure patient safety, several safeguards are in place. First, hemodynamically unstable patients are excluded from participation. Second, a referral threshold of 4 ng/L is applied (well below the 99th percentile) to minimize the risk of missed cases. Third, internal safety monitoring in complemented by an independent auditing monitor who conducts regular site visits to participating (OOH-PC) centers and performs random inspections of data management procedures. The monitoring body has full excess to the study data at all times. Lastly, an independent Data Safety Monitoring Board (DSMB) has been appointed to oversee patient safety, including monitoring of false negatives and serious adverse events, as well as the adequacy of participant enrollment. Enrollment is continuously monitored at each participating site. If inclusion rates decline, the study team will visit the site to identify barriers and provide support. We will also provide regular updates on recruitment progress with sites, and small incentives are offered upon reaching predefined enrollment milestones.

## Patient and public involvement statement

A representative from Harteraad, the patient advisory council for individuals with heart disease, was actively involved in the study design, protocol development, and the creation of patient information materials.

## Access to data

Access to the final study dataset will be limited to the principal investigators and designated members of the research team. Any request for access to the dataset or statistical code must be approved by the study's principal investigators and will require a formal data-sharing agreement to ensure data protection and integrity.

## Ancillary and post-study care

If participants experience harm related to the study, they will be referred for appropriate medical care, and compensation claims will be handled by the study's insurance, in compliance with Dutch regulations.

## Data Availability

No data was used for the research described in the article.
